**Secondary outcome:**

1-clinical improvement and hospital discharge [ Time Frame: from the date of assignment until the date of hospital discharge for the last assigned case, whichever comes first, assessed up to two months ]

2-Time of discharge from hospital after full recovery

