## **Scientific Background:**

### **COVID 19 Pathogenesis:**

COVID 19 Coronavirus disease (COVID-19) is caused by SARS-COV2 and represents the causative agent of a potentially fatal disease that is of great global public health concern(1, 2).

Patients infected with COVID-19 showed higher leukocyte numbers, abnormal respiratory findings, and increased levels of plasma pro-inflammatory cytokines(1-3). Additionally, a value of 16.16 mg/L of blood C-reactive protein was noted which is above the normal range (0–10 mg/L)(2). Patients infected with COVID-19 showed higher leukocyte numbers, abnormal respiratory findings, and increased levels of plasma pro-inflammatory cytokines. Significantly high blood levels of cytokines and chemokines were noted in patients with COVID-19 infection that included IL1- $\beta$ , IL1RA, IL7, IL8, IL9, IL10, basic FGF2, GCSF, GMCSF, IFN $\gamma$ , IP10, MCP1, MIP1 $\alpha$ , MIP1 $\beta$ , PDGFB, TNF $\alpha$ , and VEGFA(1) The latest report shows the number of CD4+ and CD8+ T cells in the peripheral blood of SARS-CoV-2-infected patients significantly is reduced, Similarly, the acute phase response in patients with SARS-CoV is associated with severe decrease of CD4+ T and CD8+ T cells(3). The report in Lancet shows ARDS is the main death cause of COVID-19. Of the 41 SARS-CoV-2-infected patients admitted in the early stages of the outbreak, six died from ARDS(3). Main mechanism for ARDS is the cytokine storm, the deadly uncontrolled systemic inflammatory response resulting from the release of large amounts of pro-inflammatory cytokines (3).The cytokine storm will trigger a violent attack by the immune system to the body, cause ARDS and multiple organ failure, and finally lead to death in severe cases of SARS-CoV-2 infection(1, 2) . IFN-I(IFN- $\alpha$  and IFN- $\beta$ ) has a protective effect on SARS-CoV and MERS-CoV infection, but the IFN-I pathway is inhibited in infected mice(4). n Number of total T cells, CD4+ and CD8+ T cells were dramatically reduced in COVID-19 patients, especially among elderly patients ( $\geq 60$  years of age) and in patients requiring Intensive Care Unit (ICU)(3). Statistical analysis demonstrated that T cell numbers are negatively correlated to serum IL-6, IL-10 and TNF- $\alpha$  concentration, potential therapeutic targets preventing cytokine storm.

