#### **Gum Arabic as anti-inflammatory agent:**

Gum Arabic anti-inflammatory effect has been investigated in clinical trials (10,12). An anti-inflammatory effect of GA was demonstrated via the application of GA in drinking water given to rats with diabetes mellitus by a decrease of TNF $\alpha$  and IL-1 $\beta$  and increase of IL-10 (14).

Interestingly, Bovo et al. investigated the effect of GA on the complement system, as arabinogalactans are reported to be complement system modulators. The authors showed a pro-inflammatory activity of GA by activation of the classical and alternative pathways of the complement system (15). GA exerted local anti-inflammatory effects by modifying nuclear factor- $\kappa$ B (NF- $\kappa$ B) on the small intestine (12). In addition, a reduction of oxidative stress was shown after GA supplementation of drinking water in the liver tissue of rats with type I diabetes (16) and oral GA supplementation in humans suffering from sickle cell anemia (17). GA significantly increased oxidative burst/ROS production of bovine and human granulocytes in a dose-dependent manner (18,19). Similarly, arabinogalactan–protein (AGP) of GA may have pro-inflammatory properties on certain parts of the immune system(18, 20).

From all the above the main pathogenesis of COVID 19 is due to inflammatory process and cytokine storm. Gum Arabic is a prebiotic dietary fibers with proven anti-inflammatory properties and immunomodulatory agent. Nowadays, most of research have carried out on corona-virus are in the primary stages and the exact mechanisms remains unknown, infection spread and deaths are increasing in daily bases, the urge for vaccine and protective elements against the immunological response of the body against the virus is needed.

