## 5. Data analysis (Methods used for Data analysis)

**Data will be collected and coded and entered in excel sheet.**

SPSS .24 and Graph prism will be used. Paired *t* test will be used to determine statistical significance between baseline and post treatment results. *P* equal to or less than .05 will consider statistically significant. Data will be presented as means ( $\pm$ SD).

- **References:**

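### Secondary outcome 2 times discharge only in patients who fully recover, so patients who die have no value and no listed outcome names death

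*Protocol*

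**What the plan says.** The Protocol, section 4, lists one primary outcome (change in an immune response score up to four weeks) and two secondary outcomes.

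- Secondary outcome 1 is "clinical improvement and hospital discharge". Its bracketed time frame reads "from the date of assignment until the date of hospital discharge for the last assigned case, whichever comes first, assessed up to two months".
- Secondary outcome 2 is "Time of discharge from hospital after full recovery". It has no time frame, no definition of full recovery, and no rule for patients who die or remain in hospital.

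Death is not among the listed outcomes. Section 5 (Data analysis) names a summary, "Data will be presented as means" with SD, and a paired t test, of which it says "test will be used to determine statistical significance between baseline and post treatment results".

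Deaths are foreseeable on the protocol's own account. The Introduction describes fatal multi-organ failure in severe disease, and the pathogenesis section reports six ARDS deaths among 41 early patients. Eligibility runs from age 8 to 90. The only exclusion that bears on severity is intubation with parenteral treatment (printed as parental).

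**The concern.** Randomisation makes the arms comparable at entry. An outcome that exists only for those who later recover gives that up, because recovery may itself depend on treatment. Each arm is then represented by its own recovered patients, and those two subsets need not be alike.

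The direction of the error matters. Patients who die are likely to be those who would have stayed longest. Removing them shortens the average stay of those left, so an arm with more deaths can appear to discharge patients sooner. Because death is not listed as an outcome, nothing beside this result would alert the reader.

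The time frame of outcome 1 raises a second, independent question. One patient's follow-up cannot sensibly end when a different patient goes home, and the phrase that selects the earlier date does not say clearly which dates are compared.

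**Working it through.** The protocol gives no sample size, expected mortality, length of stay or severity mix for this trial, so there is no planned figure to reproduce. What can be checked is the direction of the bias, and its size under stated assumptions.

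**Assumptions (none from the protocol, except that day 60 approximates its two-month limit)**
- Mean discharge day is 10 in mild and 20 in severe patients, the same in both arms, so treatment has no effect on speed of recovery.
- s is the share of severe patients, and d is the risk of death among them. Only severe patients die.
- When deaths are kept in the analysis, they are set to day 60.

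**Formulas**
- Mean among the recovered: [(1 − s)·10 + s(1 − d)·20] / [(1 − s) + s(1 − d)]
- Mean over all randomised: (1 − s)·10 + s[(1 − d)·20 + d·60]
- Proportion discharged by day 60: 1 − s·d

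The first expression equals 10 + 10·p, where p = s(1 − d) / [(1 − s) + s(1 − d)] is the share of severe patients among the discharged. Since p falls as d rises, the recovered-only mean must fall as deaths rise under these assumptions.

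**Example: s = 30%, d = 20% in control and 40% in treated (overall mortality 6% and 12%)**
- Recovered only, control: (7 + 0.3·0.8·20)/0.94 = 11.8/0.94 = 12.55 days.
- Recovered only, treated: (7 + 0.3·0.6·20)/0.88 = 10.6/0.88 = 12.05 days. The treated arm looks 0.51 days faster (from unrounded means).
- All randomised, control: 7 + 0.3·(16 + 12) = 15.4 days.
- All randomised, treated: 7 + 0.3·(12 + 24) = 17.8 days. The treated arm is 2.4 days worse.
- Discharged by day 60: 94% and 88%.

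**Range (control d = 20%)**

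| s | treated d | false gain, recovered only (days) | true loss, all randomised (days) |
|---|---|---|---|
| 10% | 30% | 0.09 | 0.4 |
| 10% | 60% | 0.39 | 1.6 |
| 30% | 40% | 0.51 | 2.4 |
| 30% | 60% | 1.09 | 4.8 |
| 50% | 30% | 0.33 | 2.0 |
| 50% | 60% | 1.59 | 8.0 |
| any | 20% | 0 | 0 |

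A simulation with gamma-distributed stays (400,000 patients per arm, s = 30%, d = 20% and 60%) agrees. Recovered-only means were 12.5 and 11.5 days, means with deaths at day 60 were 15.4 and 20.2 days, and 93.9% and 82.0% were discharged by day 60.

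**Time frame of outcome 1.** It starts at assignment, which works for each patient. Its first end date is the discharge of the last patient assigned, which does not describe any other patient's course. The two-month limit is the only part that can close an individual's follow-up. Scheduled assessments stop at week 4, so nothing in the visit plan collects status between week 4 and two months.

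**The case against.** The strongest reply is that handling of deaths, censoring and the test for a secondary time outcome commonly sit in a statistical analysis plan, which is not shown. That is fair for the method. It does not rescue the definition: what the outcome measures, and in whom, is fixed in the protocol, and there it depends on recovery.

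A reader might infer several stronger things that the documents do not support.

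- *That the time frame tied to the last assigned patient governs outcome 2 and removes the deaths.* That bracket belongs to outcome 1. Outcome 2 loses deaths through its recovery condition alone.
- *That follow-up under outcome 1 has no limit per patient, or conflicts with the four-week study.* The two-month cap can be read as each patient's own, and a discharge window longer than the treatment period is ordinary.
- *That excess deaths could not show in any outcome.* If outcome 1 were analysed as a proportion of all randomised patients, deaths would lower it. However, no denominator is stated, and a death would look the same as a long stay.
- *That the paired t test is planned for discharge time.* Section 5 confines it to baseline against post-treatment results.
- *That gum arabic is harmful.* The remark "The authors showed a pro-inflammatory activity of GA" concerns complement activation, and the same section concludes that the product is anti-inflammatory.
- *That background mortality fixes the size of the bias.* The worldwide ratio (195387/2744744 = 7.1%) and the early cohort (6/41 = 14.6%) describe different populations and cannot stand for the two arms.

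**Conclusion.** The point holds for the definition of secondary outcome 2. It is conditioned on an event after randomisation, it leaves patients who die or do not recover without a value, and no listed outcome names death. Only the direction of the bias is established, and only if mortality differs between arms and deaths fall mainly among patients who would have recovered slowly. The false gain of about 0.1 to 1.6 days rests on assumed stays of 10 and 20 days, a severe share of 10% to 50%, and death risks among severe patients of 20% against 30% to 60%. With equal mortality it is zero. The time frame of outcome 1 is a separate wording defect. Both concern secondary outcomes and should be corrected; neither affects the definition of the primary outcome.

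**What to change.** - Redefine secondary outcome 2 as time from randomisation to discharge alive, in all randomised patients, each followed to a fixed limit of two months (day 60). Keep patients who die as never discharged: treat death as a competing event, or censor at day 60 and not at the date of death. This also removes the need to define full recovery.
- Compare the arms by cumulative incidence of discharge, with a Gray or log-rank test stratified by the age and sex strata used at randomisation. This may be placed in the analysis plan, provided that the protocol carries the definition.
- Report deaths by arm over the same 60 days.
- In the time frame of outcome 1, replace the reference to the last assigned patient, and the tie-break phrase after it, with each patient's own discharge, death or two months.

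The cost is protocol wording. Discharge and death dates should be in hospital records. The small downside is a status check at day 60 for patients not discharged by week 4.

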## 5. Data analysis (Methods used for Data analysis)

**Data will be collected and coded and entered in excel sheet.**

SPSS .24 and Graph prism will be used. Paired *t* test will be used to determine statistical significance between baseline and post treatment results. *P* equal to or less than .05 will consider statistically significant. Data will be presented as means ( $\pm$ SD).

- **References:**

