## Part2

### 1. Title of Proposal:

# **Protective effect of Gum Arabic (*Acacia Senegal*) supplementation on immune responses and inflammatory markers among COVID 19 Patients**

## **Double Randomized two arms clinical trial**

### Introduction:

COVID 19 Coronavirus disease (COVID-19) is caused by SARS-COV2 and represents the causative agent of a potentially fatal disease caused global public concern. The disease spreads rapidly compared to the previous pandemics, which makes it more difficult to contain. Due to this, there is an urgent need for fast diagnosis, preventive and therapeutic measures. Patients infected with COVID-19 showed higher leukocyte numbers, abnormal respiratory findings, and increased levels of plasma pro-inflammatory cytokines. Main mechanism for ARDS (Acute Respiratory Distress Syndrome) is the cytokine storm, uncontrolled systemic inflammatory response resulting from the release of pro-inflammatory cytokines. The cytokine storm will trigger a violent attack by the immune system to the body, cause ARDS and multiple organ failure, and finally death in severe cases. Current investigations, demonstrated that T cell numbers are negatively correlated to serum IL-6, IL-10 and TNF- $\alpha$  concentration, and proposed T cells as potential therapeutic target.

Butyrate, is an epigenetic regulator via its capacity to act as a histone deacetylase (HDAC) inhibitor. This may be directly relevant to the modulation of covid-19 infection. Although data on the biological interactions of covid-19 with human physiology have still to be published, HDAC inhibition is a common regulator of the effects of many viruses, including the influenza virus. The inhibition of HDAC1, as induced by butyrate, decreases influenza-driven pneumonia infections.

Gum Arabic (GA) is a safe dietary fibres approved by FDA and WHO. It is high molecular weight polysaccharide retrieved from *Acacia Senegal* and *Acacia Seyal* trees. GA fermentation produced short chain fatty acids mainly propionate and butyrate. Gum Arabic has anti-inflammatory effect

which has been investigated in various diseases and conditions.

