#### **Specific objectives:**

- 1- To understand the immune response of disease progression and physiological pathway in patients consuming Gum Arabic (Acacia Senegal) for one month.
- 2- To study the innate and acquired mechanisms of defense against the coronavirus (cytokine and antibody responses) in placebo and experimental groups in each.
- 3- To assess clinical progression of the disease in group treated with Gum Arabic (Acacia Senegal)
- 4- Measure the level of anti-inflammatory marker (CRP & TNF $\alpha$ , IL6, IL10, IF $\gamma$ ) before and after GA ingestion

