**Method:**

**Study design:** Double blind, randomized placebo controlled clinical trial Phase III.

The study will be conducted on patients with COVID 19 infection for 4 weeks.

**Study setting:** The study will be conducted in Khartoum Isolation centers and Soba hospital Khartoum State Sudan

**Sample size:** All Patients who presented to Gabra and Soba hospital and confirmed with COVID 19 during the study period will be included after satisfying the inclusion criteria

**Study population:** (inclusion and exclusion criteria)

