**Randomization and blinding:**

The subjects, after stratification by age and sex, will randomly assigned to receive coded and indistinguishable Gum Arabic or placebo. Randomization will be conducted by using a sequence of computer-generated random numbers by independent individual.

Each participating center will be assigned a special code generated by the computer. The

randomization will be kept by the PI and a research assistant. The assessor for clinical outcomes would be blinded to the randomization status. The research staffs who perform the intervention would not know the assessment results. After the eligibility assessment by viral screening, laboratory and clinical assessments would be conducted at the baseline (after completion of informed consent), at first, second and 4th week

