**Gum Arabic administration:**

GA in powder form, it is a 100% natural extract powder produced mechanically from the wildy grown Acacia Senegal tree with a particle size less than 210 µm. The daily dose is 45 gram per day. It will be given in one sachet to be consumed in the early morning dissolved in 200 ml of water. The GA will be provided to the participants weekly for four weeks (7 sachets for each visit). Standardized questionnaire and check list will be used to collect data about patients' physical examination, weight, height, severity of the symptoms and any side effects. Gum Arabic will be purchased from nature gum company, Khartoum Sudan.

Placebo will be pectin one gram per day. It will be given in one sachet to be consumed in the early morning dissolved in 200 ml of water for 4 weeks.

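### The only significance test in the protocol is a within-patient before-after paired t test, so the randomised comparison with placebo is never tested and natural recovery can pass for a Gum Arabic effect

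*Protocol*

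**What the plan says.** The design is stated three times. The title calls the study a "Double Randomized two arms clinical trial". Section 4 (Study design) calls it a "Double blind, randomized placebo controlled clinical trial Phase III". Under Randomization and blinding, patients are stratified by age and sex and then "randomly assigned to receive coded and indistinguishable Gum Arabic or placebo".

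The analysis does not follow that design. Section 5 (Data analysis) names one inferential method, a paired *t* "test will be used to determine statistical significance between baseline and post treatment results", with the criterion that a P value "equal to or less than .05 will consider statistically significant". Results are to be shown as means with SD. Nothing else on inference appears in the section.

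The objectives lean the same way. Specific objective 3 looks at clinical progression in the treated group only. Objective 4 measures CRP and the cytokines "before and after GA ingestion". Objective 2 does mention both the placebo and the experimental group, but as something to be studied in each, not as a contrast. The primary outcome is a mean change from baseline in an immune response score over up to four weeks, again with no contrast between arms.

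**The concern.** A paired test within an arm has as its null hypothesis that the mean change in that arm is zero. A placebo-controlled trial is run to test whether the change differs between arms. The two hypotheses differ whenever patients would change without the study product.

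Here they probably would. The inclusion criteria take newly diagnosed, PCR-confirmed patients. The COVID 19 Pathogenesis section describes raised CRP and cytokines and reduced T cells in infection. Four weeks later many of these values can be expected to have moved through natural course, regression to the mean or other care. A before-after test counts all of that as signal, and the placebo arm, which exists to remove it, plays no part in the test. A report that followed section 5 could present ordinary recovery as evidence of efficacy from a Phase III trial.

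**Working it through.** The protocol states no sample size, SD, effect size or power, so there is no figure of its own to reproduce. The check asks how often the planned test is significant when Gum Arabic has no effect.

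**Inputs from the protocol:** two arms; paired t test of baseline against post-treatment; significance at 0.05.

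**Assumptions:** two-sided test; 1:1 allocation; normally distributed change scores; n = 20 to 100 per arm; the same natural shift in both arms, d = 0.2 to 0.8, where d is the mean change divided by the SD of the change; true Gum Arabic effect zero.

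**Step 1, paired test in the Gum Arabic arm.** The statistic is mean change / (SD of change / √n). It follows a noncentral t distribution with n − 1 degrees of freedom and noncentrality d√n. The rejection rate is the probability that its absolute value exceeds the 97.5% point of the central t.

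- n = 30, d = 0.5: noncentrality 0.5 × √30 = 2.74, rate 75.4%.
- n = 50, d = 0.5: 0.5 × √50 = 3.54, rate 93.4%.
- n = 100, d = 0.5: 0.5 × √100 = 5.00, rate 99.9%.

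Significant results in the Gum Arabic arm with no true effect:

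| n per arm | d = 0.2 | d = 0.3 | d = 0.5 | d = 0.8 |
|---|---|---|---|---|
| 20 | 13.6% | 24.7% | 56.5% | 92.4% |
| 30 | 18.5% | 35.5% | 75.4% | 98.8% |
| 50 | 28.4% | 54.8% | 93.4% | about 100% |
| 100 | 50.8% | 84.4% | 99.9% | about 100% |

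The rate is 5% only at d = 0. For any other shift it rises with n, so a larger trial makes the error more likely. Simulation with 20,000 trials per setting agreed with these figures.

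**Step 2, paired test in each arm, then compare the p values.** With p the rate from step 1, the chance that Gum Arabic is significant and placebo is not is p(1 − p). For n = 50, d = 0.3 this is 0.548 × 0.452 = 0.248, about 25% (simulated 25.0%). For n = 30, d = 0.3 it is 0.355 × 0.645 = 0.229 (simulated 23.3%). The maximum of p(1 − p) is 25%, reached at p = 0.5.

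**Step 3, between-arm test.** The expected difference in mean change is d − d = 0, so the shared recovery cancels. A two-sample t test on the same simulated change scores rejected in 4.5% to 5.5% of trials across all settings.

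**The case against.** The best defence is that the statistical analysis plan is not available and may contain a between-arm analysis, and that a protocol may leave such detail to it. Section 5 also does not call the paired test confirmatory or attach an efficacy claim to it. The first part would count if the protocol were silent. It is not silent: it states how statistical significance will be determined, and the stated method does not use the randomisation. An analysis plan that follows it inherits the fault, and one that departs from it contradicts the protocol. Either way section 5 has to change. What stands is a limit on scope: the absence of a comparison is a fact about the protocol text available, and the misreading of recovery as efficacy is an inference. Strictly, the test cannot tell the two apart.

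A second defence is that objective 2 brings in the placebo group. It does, but it asks for a description in each group and names no contrast or test. Nor can the pairing be read as Gum Arabic against placebo: patients are stratified, not matched, and section 5 says the pairs are baseline and post-treatment.

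A third point is that the error rates rest on assumed shifts and sample sizes. That is correct. The immune response score is not defined, and the protocol gives no expected course for it. The table should be read as a range, from 13.6% to about 100%. The direction does not depend on the assumptions: any non-zero natural change takes the rate above 5%.

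**Conclusion.** The concern holds. The one significance test in the protocol answers a different question from the one the randomised placebo-controlled design poses, and no Gum Arabic versus placebo comparison is named. With no true effect, and under the assumptions listed, the planned test in the Gum Arabic arm would be significant in 75%, 93% and 99.9% of trials with 30, 50 and 100 per arm at a 0.5 SD shift, and in 55% with 50 per arm at 0.3 SD. In that last setting, Gum Arabic significant with placebo not significant would arise in about 25% of trials. The exact rates depend on n and the shift, which the protocol does not give. The defect itself does not depend on them. It must be corrected before the trial can support an efficacy conclusion.

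**What to change.** Replace the paired-test sentence in section 5 with wording such as:

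> The primary analysis compares Gum Arabic with placebo at week 4 by analysis of covariance, with the week-4 value as response, arm as factor, and the baseline value, age and sex as covariates, in all randomised patients. The adjusted between-arm difference with its 95% confidence interval and two-sided p value is the basis for any efficacy conclusion. Within-arm changes are descriptive only.

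Reword specific objectives 3 and 4 as Gum Arabic versus placebo questions. Three further points make the replacement workable:

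- Name the measured variable that stands for the immune response score, since the model needs a defined response.
- Say how patients without a week-4 value are handled.
- Give time to discharge a between-arm time-to-event method. It has no baseline value, so a paired test cannot be applied to it.

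A two-sample test of change from baseline would also hold the 5% level. Covariance adjustment is suggested because it uses the baseline value and the stratification factors.

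The cost is protocol wording. No new measurement is needed, and the analysis runs in the software already named. The change itself adds no patients, but the protocol states no sample size, so whether recruitment will suffice for a between-arm comparison is unknown. For scale, n per arm = 2(1.960 + 0.842)² / (effect in SD)² at 80% power and two-sided 0.05 gives 175 for an effect of 0.3 SD, 63 for 0.5 SD and 25 for 0.8 SD. These effects are assumed for illustration.

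### The only test and summary in section 5, a paired t test against baseline and mean ±SD, do not fit hospital discharge or time to discharge and cannot compare the arms on them

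*Protocol*

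**What the plan says.** Section 5 (Data analysis) is the protocol's whole statement of method. It names a paired t test that "will be used to determine statistical significance between baseline and post treatment results", a threshold of P "equal to or less than .05 will consider statistically significant", and one form of summary: "Data will be presented as means" with SD. The summary is not restricted to any type of variable. No method for a proportion or a time to event is named, and no test between the arms.

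Section 4, under Secondary outcome, lists two items:
- Outcome 1 is "clinical improvement and hospital discharge", with a time frame that ends in "assessed up to two months".
- Outcome 2 is "Time of discharge from hospital after full recovery", with no time frame of its own.

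The study design entry in section 4 describes a double-blind, randomised, placebo-controlled trial, and states: "The study will be conducted on patients with COVID 19 infection for 4 weeks". Specific objective 3, in section 3, is to assess clinical progression in the group given Gum Arabic.

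**The concern.** A paired t test needs two measurements of the same quantity in each patient. Discharge happens once, after assignment, and time to discharge is one number per patient. There is no pre-treatment value to subtract. Forcing the test onto these outcomes asks only whether patients leave hospital at all, which is not the trial's question.

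Mean ±SD raises a second problem. A patient still in hospital when follow-up ends has no discharge time, only a lower bound for it, and section 5 does not say what to do. A mean of the observed times silently drops that patient, and such patients have the longest stays. If one arm recovers more slowly, that arm loses more of its long stays and looks closer to the other arm than it is.

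At stake is objective 3. These are the only clinical outcomes listed, and the stated method gives no valid comparison of the arms on discharge or on time to discharge.

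**Working it through.** The protocol gives no sample size, discharge rate, length of stay or target difference, so it has no figure to reproduce. Two checks show what the stated method would do.

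**Check 1: paired t test on a discharge indicator**

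Inputs: the test and the .05 threshold from section 5 (two-sided assumed). The coding is an assumption: 0 for everyone at baseline, 1 if discharged later. Numbers per arm are assumed.

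With k discharges among n patients, the mean difference is k/n and its squared standard error is k(n−k)/[n²(n−1)]. Hence

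t = √[k(n−1)/(n−k)], on n−1 degrees of freedom.

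- n = 20, k = 3: t = √(3×19/17) = 1.83, P = .083.
- n = 20, k = 4: t = √(4×19/16) = 2.18, P = .042.
- n = 50, k = 4: t = √(4×49/46) = 2.06, P = .044.
- n = 100, k = 4: t = √(4×99/96) = 2.03, P = .045.

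So 4 discharges in an arm suffice at each of these sizes. The chance of that within one arm, with no treatment effect, is the binomial probability of 4 or more:
- n = 20: 89% if 30% are discharged, 99.9% if 50% are.
- n = 50: 99.997% if 30% are discharged.

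The result reflects ordinary recovery. It carries no information on Gum Arabic against placebo.

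**Check 2: mean time to discharge with some patients still in hospital**

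Assumptions, none from the protocol: exponential times, no deaths, medians of 21 and 14 days. Cut-offs c: 60 days, for the two months attached to outcome 1, and 28 days, for the 4-week study period, as a sensitivity value.

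Let m = median/ln 2, giving m = 30.3 and 20.2 days. The true difference in means is 10.1 days.

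*Undischarged patients dropped.* The mean among those discharged by c is m − c/(e^(c/m) − 1).
- c = 60: 30.3 − 9.6 = 20.7 and 20.2 − 3.2 = 17.0; difference 3.7 days before rounding.
- c = 28: 30.3 − 18.4 = 11.9 and 20.2 − 9.3 = 10.9; difference 1.0 day.

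*Undischarged patients kept, stay entered as c.* The mean is m(1 − e^(−c/m)).
- c = 60: 26.1 and 19.2; difference 6.95 days.
- c = 28: difference 3.13 days.

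The size depends heavily on the assumptions. Share of the true mean difference that remains, for discharge rate ratios of 1.3 to 2.0:

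| Slower-arm median (days) | Capped, day 60 | Dropped, day 60 | Capped, day 28 | Dropped, day 28 |
|---|---|---|---|---|
| 7 | 99% | 94–97% | 82–88% | 54–65% |
| 10 | 95–97% | 80–87% | 65–73% | 32–43% |
| 14 | 85–90% | 58–69% | 47–56% | 18–26% |
| 21 | 66–74% | 33–44% | 28–36% | 9–13% |

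Simulated power at day 60 (2,000 trials, 100 per arm assumed):

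| Medians (days) | t test, dropped | t test, capped | Log-rank |
|---|---|---|---|
| 21 v 14 | 37% | 75% | 77% |
| 14 v 10 | 42% | 61% | 62% |
| 10 v 7 | 59% | 67% | 67% |

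Dropping patients costs power. Capping at two months costs 0 to 2 points, because the spread shrinks along with the difference.

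**The case against.** The strongest reply is that the t-test sentence limits itself to results that have a baseline and a post-treatment value. That describes the laboratory markers of objective 4 and the change-from-baseline primary outcome. On this reading the protocol is silent on the secondary outcomes, and a statistical analysis plan that is not shown may supply the method. Part of this stands: nothing says that the paired test will be run on discharge. But section 5 sets out the methods for the trial, its mean ±SD sentence carries no such limit, and it names nothing else. A later plan with a suitable method would be filling a gap or departing from the text.

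Several stronger readings are tempting and not supported:
- *The discharge result is always significant.* This needs a 0/1 coding that the protocol does not state, and at least 4 events in the arm.
- *The discharge-time difference is strongly attenuated.* This needs undischarged patients to be dropped, together with long stays or an early cut-off. With capped stays at 60 days and medians of 7 to 14 days, the mean difference loses only about 1–15%. The power figures for t tests also describe a between-arm comparison that section 5 does not name.
- *Both outcomes have a cut-off.* The two-month limit is attached to outcome 1 only.
- *Neither outcome has any baseline.* This is exact for discharge and time to discharge. Clinical improvement could have one, because symptom severity is recorded (section 4, Gum Arabic administration) and clinical assessments are scheduled at baseline (Randomization and blinding).

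**Conclusion.** The point holds as a mismatch between the type of data and the stated method. It covers the discharge part of outcome 1 and all of outcome 2. The paired t test has nothing to pair there, and mean ±SD has no place for a patient not yet discharged, so section 5 as written cannot show whether the arms differ on either. That conclusion needs no assumed figure.

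The sizes are conditional. The 4-discharge threshold rests on 0/1 coding and a two-sided .05 test. The fall from 10.1 days to 3.7 or 1.0 rests on exponential times, no deaths, medians of 21 and 14 days, and dropping undischarged patients. With short stays and a two-month cut-off the loss is small. The protocol has no figures to say which case applies, so it would be wrong to infer that most of a real difference would be lost. These are secondary outcomes, and the change is worth making because the remedy costs almost nothing.

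**What to change.** In section 5:
- Limit the t test and mean ±SD to the continuous markers.
- For outcome 1, compare between the randomised arms the proportion improved and discharged by a fixed day, as a risk difference with 95% CI.
- For outcome 2, state a cut-off, for example the two months already given for outcome 1. Measure time from assignment to discharge and count patients not discharged by the cut-off as censored.
- Compare the arms on outcome 2 with Kaplan-Meier or cumulative-incidence curves and a log-rank-type test, and report medians. Cumulative incidence is the better choice if deaths in hospital occur, because a patient who has died can no longer be discharged.

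Other between-arm methods that keep undischarged patients in the analysis would also do. The cost is a few sentences. No new data, visits or patients are needed, and SPSS, which the protocol already names, can run these analyses.
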